### 2.6. Intervention

At baseline, both the MR and control group will receive diet consultation and printed diabetic education material from a research dietician. On top of that, the MR group will receive a meal replacement to replace one meal daily for 5 days a week. The duration of the intervention will be 12 weeks. All participants are required to return to the clinic in the 6th and 12th week for a post-intervention assessment. A final visit will be conducted in the 48th week for a sustainability assessment.

#### 2.6.1. Meal Replacement Arm (MR Group)

On top of dietary consultation, a diabetes-specific meal replacement will be provided without any charge for the participants in the MR group. The meal replacement we have chosen for this study is a nutritionally balanced liquid meal replacement product (Metabolic Sauver) specifically developed for patients with diabetes, which is formulated and produced by *Powerlife (M) Sdn Bhd,, Kuala Lumpur, Malaysia*. It is a low glycemic indexed (GI) drink with a GI of 26.84, which aims to improve the glycemic control of T2DM patients based on a combination of dietary fibre, slow-release carbohydrate isomaltose, and various plant extracts [18,20,21]. One of the main plant extracts in the meal replacement is cinnamon extract (*Cinnulin MS*), which has been shown to improve anthropometric parameters, glycemic control, and lipid profiles of T2DM patients [22,23]. A detailed nutrition sheet on Metabolic Sauver has been included in Supplementary File 2, as has a table on the effects of some of the components in the formulation on obesity and T2DM.

Participants will be given instructions on how to prepare the meal replacement. A total of 75 g of meal replacement powder (as suggested by the manufacturer) will be dissolved in 300 mL of water to replace one meal of their choice (breakfast, lunch, or dinner). One serving of a meal replacement provides 327 kcal, 37.2 g carbohydrate, 16.2 g protein, and 14.4 g fat, and the participants are required to consume it for 5 days a week.

Participants are free to consume other meals at their will and continue their routine medical care without any changes. We believe that by enabling the participants to have flexibility in choosing their own mealtimes, their compliance with the meal replacement will be improved.

#### 2.6.2. Control Arm (DC Group)

Participants will receive one session of dietary consultation and education at baseline. The 90-min session will be conducted via a one-on-one basis by a research dietitian. The dietary consultation session mirrors usual/standard practice for diabetes patients at our local healthcare centres, including topics on calorie intake and carbohydrate requirements, carbohydrate food sources, carbohydrate exchange counting, sucrose intake, fat intake, Healthy Food Plate Malaysia, physical activity recommendation, and individualised menu plan.

Upon completion of the dietary consultation session, participants in the control group will be advised to continue their daily lives and routine medical care without extra intervention.

#### 2.6.3. Follow-Up

On the 6th and 12th week, all participants will return to the clinic for an outcome measures assessment. Upon completion of the intervention, participants will be monitored without any intervention for an additional 36 weeks. A final visit to the clinic will be conducted on the 48th week. During these last two visits, a similar assessment on the outcome measures will be carried out to determine the sustainability effect of meal replacement interventions.

### 2.7. Compliance and Adverse Effects Monitoring

A daily checklist will be handed out to the participants to monitor compliance with the meal replacement. Daily reminders will be sent through the WhatsApp application to remind the participants to ensure their compliance with the meal replacement. Non-responsive participants will be contacted through a phone call for an additional reminder. The participants in the treatment group will be required to bring along the meal replacement container during the follow-up visit to the clinic. Compliance will be assessed by comparing the daily checklist and the remaining meal replacement powder.

Participants will be considered non-compliant if they miss more than 30% of meal replacement intake throughout the intervention period. Participants will also be asked to report any complications or adverse effects, and this information will be recorded on an adverse effect sheet. Any occurrence of adverse events due to trial intervention will be reported to the clinic and attended to by a medical doctor from the research team if any treatment is needed.

### 2.8. Data Collection and Outcome Measurement

All participants are required to attend the clinic at baseline, 6th, 12th, 24th, 36th, and 48th week for data collection (Table 3).

#### 2.8.1. Socio-Demography Information

Participants will complete a demographic questionnaire during the screening process. The name, age, and gender of the participants will be recorded on their identification cards. Details such as ethnicity, phone number, address, marital status, number of children, educational status, years of formal education, occupation, and household income will be obtained through the questionnaire. The presence of pre-existing medical condition(s) and medical treatment(s) will be based on medical records presented by the participants and self-reports. Participants will also be asked about their habits on smoking and consumption of alcoholic beverages.

#### 2.8.2. Physical Activity Assessment

A validated Malay version of the Global Physical Activity Questionnaire [24] will be used to determine the physical activity level of the participants. The metabolic equivalent and total daily energy expenditure of the subject will be calculated based on the questionnaire’s guidelines.

#### 2.8.3. Dietary Assessment

An experienced research dietitian will be carrying out the dietary assessments on each participant at the beginning of the study. A 3-day dietary record will be used to monitor the dietary intake of the participants throughout the study period [25]. In the 3-day dietary record, food and drinks consumed by the participants for 2 weekdays and 1 day of the weekend in a week will be recorded. Participants will be asked to provide as much detail as possible on the meals taken, such as type and amount consumed, method of preparation, brands of food, sauce, and ingredients used. Participants will be shown pictures of various household measurements based on the Atlas of Food Exchanges & Portion Sizes to help them estimate the portion size [26]. Any supplements such as vitamins or minerals consumed will also be recorded. In addition, a specific modified validated food frequency questionnaire (FFQ) on added sugar food/drinks from Norimah AK [27] will also be used to identify the types, frequency, and quantity of added sugar to the food or drink consumption among participants. Computer-based analysis of mean caloric and nutrient intake will be performed using the Nutritionist Pro software (Axxya Systems, Stafford, TX, USA).

#### 2.8.4. Anthropometry Measurements

Anthropometric measurements will be conducted based on the procedures described by Gibson [28] and WHO [29]. We will be measuring weight, height, body composition (muscle mass, fat mass, and fat percentage), neck circumference, waist circumference, and hip circumference. Body mass index (BMI) will also be calculated.

Weight will be measured by using the Tanita HD-309 (Tanita Corporation, Tokyo, Japan) weighing scale. The standing height of the participants will be measured using a stadiometer to the nearest 0.1 cm, and BMI will then be calculated. Neck, waist, and hip circumference will be measured by using a soft measuring tape to the nearest 0.1 cm. The waist-hip ratio will be calculated by dividing the waist by the hip circumference.

Body composition will be measured by using bioelectrical impedance analysis with a body composition analyser (Model; SC-330, TANITA Japan) [30,31,32,33]. Muscle mass (kg), fat mass (kg), and fat percentage (%) will be extracted and copied into the database.

All anthropometry measurements will be conducted in duplicates, and mean readings will be calculated.

#### 2.8.5. Visual Analog Scale for Satiety Measurement

A Visual Analog Scale (VAS) questionnaire will be used to assess the participant’s perceived satiety after the consumption of the meal replacement in the treatment group or the consumption of a meal in the control group [34].

Participants will be instructed to fill up the VAS just before they consume a meal/meal replacement, 30 min, 60 min, 120 min, 180 min, and 240 min after meal consumption. An average appetite score will be calculated at each time of measurement by using the formula as shown below [35].

Average appetite = desire to eat + hunger + (10−fullness) + prospective food consumption.

#### 2.8.6. Blood Pressure

Ambulatory blood pressure will be measured using an electronic blood pressure machine (Omron Corporation, Kyoto, Japan).

#### 2.8.7. Metabolic Profiles

Blood samples of the participants will be collected by a qualified phlebotomist at baseline, on the 12th week and the 48th week. Prior to the day of blood collection, participants will be reminded to fast for eight hours (only plain water is permitted). After that, a total of 7.5 mL of venous blood sample will be taken for biochemical analysis. Blood will be transferred into their respective types of vacutainers and delivered to a certified diagnostic laboratory (Lablink (M) Sdn Bhd, Kuala Lumpur, Malaysia; MS-ISO 15189) for analysis. The results of the blood test will be mailed or given to the participants during the next follow-up. Contact details are provided along with the results to enable the participants to contact the investigators or physician if they have any inquiries. The biochemical parameters measured are listed below:

aHbA1c

Blood samples will be collected in an EDTA tube and measured using an automated high-performance liquid chromatography analyser Adams A1c HA-8180V (Arkray, Tokyo, Japan).

bFasting Blood Glucose

Blood samples will be collected in a sodium fluoride tube and measured using an automated photometric analyser ARCHITECT c16000 and c8000 (Abbott Laboratories, North Chicago, IL, USA).

cFasting Insulin Level

Blood samples will be collected in a serum separator tube, and the fasting insulin level is measured using an automated chemiluminescent analyser (Advia Centaur XP Immunoassay System, Siemens, USA). Insulin resistance index (HOMA-IR) is calculated according to the formula: fasting insulin (micro U/L) × fasting glucose (nmol/L)/22.5 [36].

dLipid Profile Test

Total cholesterol, HDL cholesterol, LDL cholesterol, and total glycerides will be analysed. Blood samples will be collected in a plain tube and measured using an automated photometric analyser ARCHITECT c16000 and c8000 (Abbott Laboratories, USA).

eLiver Profile Test

Total protein, albumin, bilirubin total, Alkaline Phosphatase (ALP), and Alanine Amino Transferase (AST) will be analysed. Blood samples will be collected in a plain tube and measured using an automated photometric analyser ARCHITECT c16000 and c8000 (Abbott Laboratories, USA).

fRenal Profile Test

Potassium, sodium, urea, creatinine will be analysed. Blood samples will be collected in a sodium fluoride tube and measured using an automated photometric analyser ARCHITECT c16000 and c8000 (Abbott Laboratories, USA). The estimated glomerular filtration rate will be calculated with the creatinine levels obtained.

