### 2.9. Statistical Analysis

Statistical Package for the Social Sciences (SPSS) program version 23.0 will be used to analyse the data. The data will be presented as mean ± SD for parametric data and median (range) for non-parametric data. The normality of data distribution will be tested using the Shapiro–Wilk test. A *p*-value of <0.05 will be used to denote statistical significance. Descriptive analysis including frequencies, percentage, mean, and standard deviation will be used to analyse sociodemographic data and blood pressure.

For the effects of meal replacement on metabolic profiles, anthropometric measurements, satiety levels, hormonal changes, and QoL scores, mixed-design ANOVA will be used to compare between the intervention group and the control group to determine the interaction effect of intervention and time.

To determine the cost-effectiveness, incremental cost-effectiveness ratios (ICER) will be calculated by dividing the difference in total costs (between control and treatment) with the difference in the chosen measure of health outcome or effect (QALY). To assess the sustainability of the meal replacement, mixed-design ANOVA will be used to compare clinical parameters and hormonal level changes between groups on week 12 and week 48.

The main analysis will be conducted in the intention-to-treat (ITT) population in which missing values will be predicted by using the estimating equation method by adapting statistical models to the data observed using the missing-at-random method. Complete case analysis will also be performed in the per-protocol (PP) population.

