## 3. Impact of COVID 19 on Data Collection

### Preliminary Result

The study is currently in the recruitment and initial intervention phase. A total of 5185 patients were screened between September 2020 to May 2021 from digital medical records. A total of 136 participants were identified to be recruited. The intervention process has not yet been started. The overall distribution of participants identified by gender, age, and race is shown in Table 4 below. The overall mean age (±SD) of the participants is 54.9 ± 9.3 years. Among them, there are 81 males and 55 females with predominantly 63.97% Malay, 18.38% Chinese, 15.44% Indian, and 0.02% others. Overall, HbA1c levels of the participants averaged 8.5 ± 1.0%, while fasting plasma glucose levels averaged 8.6 ± 2.5 mmol/L.

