**Output**	
Noncentrality parameter λ	= 8.1087367
Critical F	= 3.9214782
Numerator df	= 1.0000000
Denominator df	= 118
Total sample size	= 120
Actual power	= 0.8063091

**Table 3 ijerph-19-04188-t003:** Data collection Table.

Data Collected/Session	Week 0	Week 6	Week 12	Week 24	Week 36	Week 48
Socio-demography information	/					
Global Physical Activity Questionnaire	/		/	/	/	/
Dietary Assessment						
3-day dietary recall	/	/	/	/	/	/
Food Frequency Questionnaire	/	/	/	/	/	/
Anthropometry Measurements						
Height	/	/	/	/	/	/
Weight	/	/	/	/	/	/
Neck circumference	/	/	/	/	/	/
Waist circumference	/	/	/	/	/	/
Hip circumference	/	/	/	/	/	/
Body composition (muscle mass, fat mass, fat percentage)	/	/	/	/	/	/
Metabolic Profiles						
HbA1c	/		/			/
Fasting Blood Glucose	/		/			/
Insulin Resistance Index (HOMA-IR)	/		/			/
Lipid profile	/		/			/
Renal Profile	/		/			/
Liver Profile	/		/			/
Hormone related to Glycemic Control						
Adiponectin, Leptin	/		/			/
Satiety Measurements						
VAS	/	/	/	/	/	/
Ghrelin, obestatin, peptide YY	/		/		/	/
Quality of life						
ADDQOL-19	/		/	/	/	/
DTSQ	/		/	/	/	/
DDS	/		/	/	/	/
Cost-effectiveness						
EQ-5D-5L	/		/	/	/	/

**Table 4 ijerph-19-04188-t004:** Sociodemographic of participants identified (n = 136).

Parameters	Numbers/Mean
Gender	
Male	81 (59.5%)
Female	55 (40.5%)
Age	54.9 ± 9.3
Race	
Malay	87 (63.97%)
Chinese	25 (18.38%)
Indian	21 (15.44%)
Others	3 (0.02%)
Duration of diagnosis for T2DM (Years)	6.4 ± 4.3
HbA1c Levels (%)	8.5 ± 1.0
Fasting Plasma Glucose (mmol/L)	8.6 ± 2.5

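### The units printed in the HOMA-IR formula do not fit its divisor of 22.5, and the glucose unit contradicts the article's own mmol/L

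*Protocol article*

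**What the plan says.** The protocol article lists HOMA-IR among the secondary endpoints (section 1.1.2) and schedules it at weeks 0, 12 and 48 (Table 3). Section 2.8.7, item c, says that "the fasting insulin level is measured using an automated chemiluminescent analyser" and then defines the index as "fasting insulin (micro U/L) × fasting glucose (nmol/L)/22.5", with a literature reference. No other place in the article says how the index is computed, and none states an insulin unit.

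Fasting glucose does appear elsewhere with a unit. Section 3 says that "fasting plasma glucose levels averaged 8.6 ± 2.5 mmol/L", and the corresponding row of Table 4 is also labelled in mmol/L.

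For metabolic profiles, the group to which Table 3 assigns HOMA-IR, section 2.9 states that "mixed-design ANOVA will be used to compare between the intervention group and the control group", with the interaction of intervention and time as the effect of interest.

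**The concern.** The divisor in HOMA-IR is a scaling constant tied to one pair of units. If the units change and the constant does not, the result is no longer on the HOMA-IR scale. The printed formula keeps 22.5 but pairs it with a glucose unit a million times smaller than the one in which the article reports its data, and with an insulin unit a thousand times smaller than the one the constant belongs to.

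This line is the operating definition of an endpoint, not background text. At stake is the reported scale of that endpoint: group means, between-group differences, their intervals, and any comparison with other studies. The article also offers no correct written definition against which the person computing the index could check the laboratory's insulin unit.

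**Working it through.** **Inputs from the article**
- Formula: insulin in micro U/L, glucose in nmol/L, divisor 22.5 (section 2.8.7, item c).
- Mean fasting glucose: 8.6 mmol/L (section 3 and Table 4).

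**Inputs not in the article**
- Standard definition of the index: insulin in micro U/mL × glucose in mmol/L / 22.5. The constant makes the index 1 at 5 micro U/mL and 4.5 mmol/L: 5 × 4.5 / 22.5 = 1.
- Fasting insulin: the article gives no value, so 5 to 30 micro U/mL is assumed, with 10 as the worked example.

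The article states no HOMA-IR value, so there is no figure to reproduce.

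**Step 1. Unit conversions**
- Glucose: 1 mmol/L = 10^6 nmol/L.
- Insulin: 1 micro U/mL = 10^3 micro U/L. Also, 1 micro U/mL = 1 mU/L, so reporting per litre in mU/L changes nothing.
- Combined inflation under the printed units: 10^6 × 10^3 = 10^9, whatever the insulin value.

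**Step 2. Worked example (glucose 8.6 mmol/L, insulin 10 micro U/mL)**

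| Units used | Calculation | Result |
|---|---|---|
| Standard (micro U/mL, mmol/L) | 10 × 8.6 / 22.5 | 3.82 |
| Both as printed (micro U/L, nmol/L) | 10^4 × 8.6 × 10^6 / 22.5 | 3.82 × 10^9 |
| Only insulin as printed | 10^4 × 8.6 / 22.5 | about 3,820 |
| Only glucose as printed | 10 × 8.6 × 10^6 / 22.5 | 3.82 × 10^6 |

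Over the assumed insulin range, the standard-unit value runs from 5 × 8.6 / 22.5 = 1.9 to 30 × 8.6 / 22.5 = 11.5. The ratio of printed to standard is 10^9 throughout.

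**Step 3. Effect on the test.** Multiplying every value by a constant k multiplies every mean square in the mixed-design ANOVA by k². The F ratios are ratios of mean squares, so they and their p-values do not change. A check on simulated data with 60 per group agreed: a two-sample t-test gave p = 0.262 before and after multiplication by 10^9. Means, differences, standard deviations and interval limits are all multiplied by k.

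**The case against.** The strongest reply is that this is a slip in unit labels with no practical effect. To obtain the inflated value, someone would have to convert 8.6 mmol/L to 8,600,000 nmol/L and 10 micro U/mL to 10,000 micro U/L before applying the formula. Nothing in the article suggests that anyone will do so: glucose is already handled in mmol/L, the formula cites a source, and the assays are run by a certified laboratory. The primary endpoints are HbA1c and body weight, the sample size rests on HbA1c, and neither the eligibility criteria nor the minimisation factors use HOMA-IR.

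Most of this stands. It makes the point minor, and a misprint is the likely explanation. It does not make the printed line correct, and that line is the only computing rule given for the endpoint.

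A reader might go further and infer that the trial will report HOMA-IR a billion times too large, or that a partial correction would leave a thousand-fold error unseen. The documents do not support either inference. No HOMA-IR value has been reported, and the article's glucose data are in mmol/L. A value near 3,800 where about 4 is expected would be noticed. Nor is insulin reported per litre a hazard in itself, because mU/L gives the correct index; only micro U/L would not, and the article does not say that the laboratory reports in that unit.

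**Conclusion.** The formula is wrong as written, and the point is minor. The two halves rest on different evidence. The glucose unit is contradicted by the article's own data, so that half needs no outside source. The insulin unit has no internal contradiction; that half rests on the standard definition of the index, to which the divisor 22.5 belongs.

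Read literally, the index is inflated by exactly 10^9, and this factor does not depend on the assumed insulin. The individual HOMA-IR values shown above do depend on it. The group-by-time test is unaffected, provided that the same units are used for every participant and visit. The primary endpoints and the sample size are untouched. The exposure is confined to the reported level, difference and interval of one secondary endpoint.

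**What to change.** In section 2.8.7, item c, state: HOMA-IR = fasting insulin (micro U/mL, equal to mU/L) × fasting glucose (mmol/L) / 22.5. Before computing the index, check the unit in which the laboratory reports insulin, and convert if it is anything other than micro U/mL or mU/L.

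The cost is one line of text and one check with the laboratory. The design, data collection and analysis method stay as they are, and no published HOMA-IR figure needs recalculating.

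### The renal profile, which includes sodium, is to be collected in a sodium fluoride tube, so the sodium result would be invalid as written (minor text correction)

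*Protocol article*

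**What the plan says.** Section 2.8.7 (Metabolic Profiles) of the protocol article sends each portion of blood to its own kind of tube: "Blood will be transferred into their respective types of vacutainers". It then names the tube for each test:

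- HbA1c: EDTA.
- Fasting glucose: "Blood samples will be collected in a sodium fluoride tube and measured using an automated photometric analyser ARCHITECT c16000 and c8000".
- Fasting insulin: serum separator.
- Lipid profile and liver profile: "Blood samples will be collected in a plain tube and measured using an automated photometric analyser ARCHITECT c16000 and c8000".
- Renal profile: "Potassium, sodium, urea, creatinine will be analysed. Blood samples will be collected in a sodium fluoride tube", on the same analysers as glucose, lipids and liver.

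The renal entry adds one use of its results: "The estimated glomerular filtration rate will be calculated with the creatinine levels obtained". Nothing elsewhere in the article names a different tube for sodium or for any other renal analyte.

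Table 3 schedules the renal profile at weeks 0, 12 and 48. On reporting, Section 2.8.7 says: "The results of the blood test will be mailed or given to the participants during the next follow-up".

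**The concern.** A tube prepared with a sodium salt puts sodium into the blood it receives. A sodium concentration measured in that blood is the participant's own sodium plus an amount from the tube. This follows from the additive's name and needs no outside source.

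The article does not leave tube choice to a fuller document. It fixes a tube test by test, and for one test the choice defeats one of the measurements.

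What is at stake is limited but real. A scheduled analyte would be unusable at three visits, or would need redrawing once the fault was noticed. The value could also be reported to participants. Because Table 3 files the renal profile under metabolic profiles, and Section 2.9 plans a mixed-design ANOVA for metabolic profiles, sodium could also enter a between-group table with values that mean nothing in absolute terms.

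**Working it through.** **Text comparison.** The protocol states no figure to reproduce, so the main check sets the Section 2.8.7 entries side by side.

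| Test | Tube named | Additive supplies the analyte? |
|---|---|---|
| Fasting glucose | Sodium fluoride | No |
| Lipid profile | Plain | No |
| Liver profile | Plain | No |
| Renal: sodium | Sodium fluoride | Yes |
| Renal: potassium, urea, creatinine | Sodium fluoride | No, on what the article names |

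All these tests run on the same analysers. The renal entry's tube-and-analyser wording repeats the glucose entry. The same section has other slips: the HOMA-IR formula gives glucose in nmol/L, and alanine amino transferase is abbreviated AST. A carry-over is therefore the likeliest explanation.

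**Size, for illustration only.** The article gives no additive concentration, so one has to be assumed.

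Inputs:
- Molar mass of sodium fluoride: 22.990 + 18.998 = 41.99 g/mol, with one sodium ion per unit.
- Assumed load: 1 to 4 mg of sodium fluoride per mL of blood.

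Formula: added sodium (mmol per litre of blood) = load (mg/mL) ÷ 41.99 × 1000.

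- 1 mg/mL: 1 ÷ 41.99 × 1000 = 23.8 mmol/L
- 2.5 mg/mL: 2.5 ÷ 41.99 × 1000 = 59.5 mmol/L
- 4 mg/mL: 4 ÷ 41.99 × 1000 = 95.3 mmol/L

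These are per litre of whole blood. If all the added sodium stayed in the plasma, and the haematocrit were 0.45 (a further assumption), each figure would be divided by 0.55, giving about 43 mmol/L at 1 mg/mL and 173 mmol/L at 4 mg/mL. The size therefore depends on the assumptions; the direction, upward, does not.

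**Effect on the comparison between arms.** Both arms use the same tube at the same visits. If every tube added the same amount d, the measured mean in each arm would be its true mean plus d, and d would cancel in the difference between arms and in change from baseline. What would not cancel is tube-to-tube variation: a fixed mass of additive in a smaller volume of blood gives a larger added concentration, so uneven filling adds noise.

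**Reach.** Sections 1.1.1 and 1.1.2 list the primary and secondary endpoints, and serum sodium is in neither. It plays no part in the sample size (Section 2.2), the eligibility criteria (Table 1) or any decision rule in the article.

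**The case against.** The strongest reply is that this is a wording slip in a condensed journal article. A qualified phlebotomist and a certified diagnostic laboratory would work from the laboratory's own collection instructions, so the wrong tube may never be filled. That may well be true, and the article cannot settle it. It lowers the weight of the point but does not remove it, because the sentence is a specific measurement instruction and is wrong as it stands.

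Four stronger readings are tempting, and the document does not support them.

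- *That the whole renal profile is invalid.* The sodium-salt argument reaches sodium only. The article names no additive containing potassium and gives nothing to show that urea, creatinine or the estimated glomerular filtration rate would be biased. The renal exclusion criterion in Table 1 is likewise not shown to be affected.
- *That a real change in sodium would be hidden.* An offset of the assumed size would probably be conspicuous in the first results, and a common offset cancels between arms. Noise from uneven filling is possible, but the article gives no basis for sizing it. Unusable values or repeat draws are the more realistic outcome.
- *That the article directs staff to this tube on home visits.* Section 4 says that a phlebotomist will take blood at home and says nothing about tubes.
- *That a safety measure is compromised.* The article classes the renal profile with metabolic profiles and does not call it a safety endpoint. It is true that there is no external monitoring board (Section 2.11) and that results go to participants, but Section 2.8.7 also provides contact details for their queries.

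**Conclusion.** The point holds for sodium: the renal entry is wrong as written. Followed literally, it makes the sodium value invalid at weeks 0, 12 and 48. This conclusion needs only the name of the additive and the list of analytes.

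The figure of about 24 to 95 mmol/L rests wholly on the assumed 1 to 4 mg of sodium fluoride per mL of blood, and should be cited only with that assumption.

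Severity is minor. The trial's main conclusions on HbA1c and body weight do not depend on this measurement, and neither do the secondary endpoints. It remains worth correcting because the fault is plain and the correction is nearly free.

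**What to change.** Check the renal entry in Section 2.8.7(f) against the laboratory's collection procedure. Change the named tube to the plain tube already drawn for the lipid and liver profiles, and keep the sodium fluoride tube for fasting glucose only. If a separate phlebotomy instruction exists, confirm that it agrees.

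The cost is a few words and one query to the laboratory; no new tube type is needed. Section 3 reports that the intervention had not yet started, so on that account the correction could precede most or all of the sampling. If any renal samples have already been drawn, record which tube was used and mark sodium as not valid for those taken into sodium fluoride.
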